# [name]

**Background**

Postpartum hemorrhage is a major cause of maternal death worldwide and is most commonly a result of uterine atony, the failure of the uterus to contract to stem blood loss following delivery. Active management of the third stage of labor (AMTSL) is recommended in high- and low-resource settings as an effective method to prevent postpartum hemorrhage secondary to uterine atony. The administration of a synthetic uterotonic stimulates the smooth muscles of the uterus to increase tone and is a major component of AMTSL that is practiced in many parts of the world. Oxytocin is universally considered the uterotonic of choice for this indication. Comparative studies of oxytocin either in combination with other components of active management or alone show that it reduces the risk of bleeding and PPH.

The published literature on the use of oxytocin to prevent PPH is relatively large, but it describes many variations in its administration (e.g. route, dose and timing). For example, in some studies oxytocin is administered intravenously (IV) ;and in others it is administered intramuscularly (IM) We are not aware of any published studies that directly compare IV and IM administration of oxytocin during the third stage of labor and the ongoing underlying assumption seems to be that the route of administration has no effect on postpartum blood loss . However, results from a 1972 study on circulating oxytocin levels after IV, IM and subcutaneous injections of Syntometrine (5 IU oxytocin and 0.5mg ergometrine) in a small sample of women in the third stage of labor (n=26) indicated that plasma oxytocin levels rise more rapidly following IV and reach a much higher peak than after IM .

These variations in route of oxytocin administration noted in the literature are also reflected in clinical practice and guidelines, and there does not seem to be agreement or a universal standard procedure for providing prophylactic oxytocin in the third stage of labor. Some guidelines specify IM administration, which is the most reasonable route for lower-levels of care and other settings where IV insertion is not feasible because of required skills/permission and because it complicates mobility and care of patients . Other guidelines either do not specify one route over another or they offer the two as equal alternatives .

It is likely that much of the variation in clinical protocols on oxytocin administration can be attributed to inadequate or disputed data on the pharmacokinetics and pharmacodynamics of oxytocin.The time to steady state plasma concentration depends on the half life of a drug. The longer the half life, the longer it takes to achieve a steady state. The half life of oxytocin is usually reported as approximately three minutes, although some articles report half-lives up to 20 minutes. Regardless of route of administration, oxytocin is fast-acting. Uterine sensitivity to oxytocin increases throughout pregnancy due to higher concentration of oxytocin receptors. After IV injection, the onset of action is almost immediate, within one minute, and a slightly slower 2-4 minutes after IM injection . With IV infusion, the uterine response is gradual and achieves steady-state plasma concentrations after 15-40 minutes ; sustained contractions, although speed of delivery characterized by needle gauge, catheter size and quantity of fluid for dilution, can affect time to steady state.

While a comparison of IV and IM administration of oxytocin during the third stage of labor has not been rigorously explored, authors of several papers question a potential effect of the route of administration, particularly in relation to speed of delivery and its effect on preventing postpartum blood loss. An unpublished secondary analysis from a large clinical trial in which women received oxytocin prophylaxis in the third stage of labor suggests that route of administration matters, particularly when oxytocin is the only AMTSL component provide. Mean postpartum blood loss was 336 ml among women who received only oxytocin IM prophylaxis in the third stage of labor (n=2845) and was 60 ml lower (277 ml) among women who received only oxytocin IV prophylaxis (n=785). The women who received oxytocin prophylaxis via IV had a reduced risk of postpartum blood loss 700ml compared to women who received oxytocin IM (OR 0.24, 95% CI 0.12-0.51). The probability of such blood loss was 0.5% instead of 2.1%. Of the 785 women who received oxytocin by IV, the vast majority of women receiving oxytocin IV were given bolus injections. Forthcoming results from a WHO-sponsored study on the components of AMTSL will include a comparison of the effect of IV and IM oxytocin on PPH. Another study found that IV bolus of oxytocin resulted in a statistically significant lower estimated mean blood loss as compared to IV infusion of oxytocin (358 ml vs 424 ml, p=0.029). In this study, blood was not measured in a calibrated container and blood loss was estimated by clinical providers’ visual assessments, however it does raise the question of whether IV bolus and IV infusion are as similar as they are assumed to be.

Oxytocin is widely considered to be a safe drug when used prophylactically to prevent PPH. Side effects are uncommon in women who deliver vaginally, however nausea and vomiting have been reported . A study comparing maternal hemodynamics after oxytocin bolus or infusion in the third stage of labor following vaginal delivery showed that bolus administration of oxytocin 10 IU is not associated with adverse hemodynamic responses and can safely be administered to women with intravenous access in the third stage of labor for postpartum hemorrhage prophylaxis.

En el presente protocolo, describimos un estudio controlado y aleatorizado que busca evaluar el efecto de la vía de administración de 10 UI de oxitocina en la pérdida promedio de sangre en hospitales de nivel terciario, donde la política de atención estándar es la administración de oxitocina profiláctica en la tercera etapa del parto. (La dosis de oxitocina profiláctica varía de 5 a 40 UI, pero dado que el uso de 10 UI es más común en varios modos de administración y es el recomendado por la Organización Mundial de la Salud, estandarizaremos una dosis de 10 UI para todos los grupos de tratamiento.) En nuestro análisis, se documentará y controlará la práctica de otros componentes del MATEP. También evaluaremos los efectos secundarios y eventos adversos asociados a cada vía de administración, incluida la pérdida de sangre.

In this protocol, we describe a randomized controlled study design that seek to evaluate the effect of route of administration of 10 IU oxytocin on mean blood loss at a tertiary-level hospital where institutional policy requires prophylactic oxytocin in the third stage of labor. (The dose for oxytocin prophylaxis can range from 5 to 40 IU, but the use of 10 IU is more common across different modes of administration and is recommended by the World Health Organization , so we will standardize a dose of 10 IU in all treatment groups.) The practice of other AMTSL components will be documented and controlled for in our analysis. We will also evaluate the side effects and adverse events associated with each route of administration, including blood loss.

The results of these studies will fill a void in the published literature about whether route of oxytocin administration during the third stage of labor has an effect on blood loss. Furthermore, the results of this study could have important implications for use of non-parenteral uterotonics as prophylaxis in the third stage of labor, such as misoprostol, an E1 prostaglandin analog that is effective in reducing acute and severe PPH. Current guidelines recommend that oxytocin delivered by IV infusion or IM injection is preferred over misoprostol, however, a difference in effectiveness of route of oxytocin administration to stem postpartum bleeding favoring IV would suggest a greater role for misoprostol where oxytocin is available but IV administration is not feasible.

Complementary to ongoing research on treatment of PPH, there is a need for evaluation of new clinical indicators that could facilitate early diagnosis and treatment of PPH. For now, timely and appropriate clinical intervention largely depends on providers’ ability to assess blood loss visually to determine whether treatment might be required. Estimating postpartum blood loss repeatedly has been shown to be difficult and inaccurate in a range of delivery settings (Schorn 2010) . Furthermore, uncertainties remain about the quantities of blood loss that are of greatest importance in predicting severe maternal outcomes for women with excessive bleeding. Some clinical signs and symptoms (such as pallor, weakness, palpitation, tachycardia, confusion, oliguria, etc) have been correlated with blood loss and may be useful for triggering clinical intervention in the management of PPH (Bonnar 2000) . A systematic review of the literature assessing the relationship between clinical signs and symptoms and blood loss with maternal outcomes suggests that a shock index, a calculated variable of heart rate to systolic blood pressure, may be a useful marker for evaluating the severity of blood loss (Pacagnella 2013). Most of the studies included in the review report an association between heart rate, blood pressure and/or shock index with blood loss. However, few of these studies were conducted among obstetric populations, in which pregnancy-induced hemodynamic changes might lead to a different relationship between clinical signs and blood loss. Thus, further research is warranted to assess the relationship between shock index and severity of blood loss during the immediate postpartum period. Recent retrospectives studies that evaluated the relationship between severe PPH and vital signs suggest that elevated levels of shock index (e.g. SI ≥ 0.9 or ≥ 1.7) can help to identify women in need of urgent .

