***Randomization and Enrollment***

All participants will be randomized to prophylactic management with oxytocin in the third stage of labor either via IV infusion or IM injection, with the assignment contained in sequentially numbered sealed opaque envelopes. During the second stage, prior to each woman’s delivery, study personnel will open the next sequential randomization packet containing her study group assignment. Since the study will be blinded and placebo-controlled, study personnel will open the next sequential drug packet, which will contain a vial each of 10 IU oxytocin and 10 IU matching placebo. Each vial will have an affixed label indicating the assigned route of administration of the contents.

10 IU oxytocin ampoules and similar placebo ampoules (containing 10 IU of saline) will be prepared by a local laboratory / pharmacist. The ampoules prepared for the study (e.g. study packets) will have to be stored in a refrigerator to maintain the cold chain necessary for oxytocin until the time of administration to the mothers. The randomization code will be generated in advance by Gynuity Health Projects staff in New York. The random assignment will be made in blocks of 10 and will be generated with a computer program. Only the Gynuity study coordinator will have access to this randomization scheme. Once an administration assignment has been allocated, the woman will be considered an enrolled participant.

Study staff will observe women and will record any intervention, including other AMTSL components performed during delivery. In addition, staff will note whether a woman has had her labor induced or augmented prior to delivery and, if possible, the drug used and time administered. In the case of labor augmentation with oxytocin, it should also be noted that the agent was discontinued upon delivery of the fetal head.

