***Intervention***

Oxytocin 10 IU will be administered either by IV infusion or IM according to randomization assignment as soon as possible after delivery of the baby.

Immediately following delivery of the baby (or last baby, in the case of multiples), blood loss will be measured in a calibrated container for 1 hour. Blood loss will be recorded when active bleeding stops or at 1 hour, whichever is later. In the case of excessive bleeding or PPH requiring treatment, blood loss will be documented also at time of diagnosis. At delivery, some blood can be expected to spatter on the drapes and on the gowns of the attendant, and all attempts will be made to minimize such losses. Additionally, the placental interstices contain maternal blood (about 9% of the placental weight). We expect that overestimations (amniotic fluid) and underestimations (blood loss) are likely to be distributed between the two study arms; therefore there will be no need for corrections to the blood measurement for these inaccuracies.

If a woman experiences excessive bleeding or PPH and requires treatment, she should receive treatment according to standard of care at the study site. If PPH is diagnosed, measurement will continue until the bleeding stops. Health providers can diagnose PPH at any time, but if blood loss reaches 500 ml according to the marking on the calibrated container, PPH should be diagnosed and standard hospital treatment initiated.

The study staff will keep the participants under observation and record all interventions performed during delivery, including the prophylactic oxytocin administration of the study. Also, note if the delivery was induced or stimulated before delivery and if possible, the medication provided, and the time and dose in which it was administered. The provider will be asked to monitor the woman for side effects for 1 hour after delivery. Women will also respond to questions about side effects prior to discharge from the hospital.

In order to document changes in shock index values during the first hour after delivery, the heart rate and blood pressure of all women enrolled at 15, 30, 45 and 60 minute intervals will be recorded. These measurements will be taken independently of the diagnosis of PPH and the exact time of each measurement will be recorded. Automatic devices will be provided to all study centers to measure blood pressure and heart rate in order to standardize such measurements.

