***Analysis and Dissemination of Results***

Bivariate analyses will be conducted, stratified by study arm. Unadjusted and adjusted logistic regression will be conducted respectively for categorical and continuous dependent variables.

To compare the two study arms (oxytocin IM vs. oxytocin infusion), the main analyses will include:

- Mean postpartum blood loss (primary outcome)
- % of women with blood loss ≥500 ml (primary outcome)
- Median postpartum blood loss and interquartile range
- % of women with blood loss ≥1000 ml,
- Mean change in Hb measured pre- to post-delivery
- % of women with postpartum Hb drops of 2 g/dl or greater
- % of women with prolonged third stage of labor
- % of women who received additional oxytocics or other interventions to manage bleeding
- % of women who experienced side effects

We will register use of any other AMTSL components, such as controlled cord traction, uterine massage, etc. that are used.

In order to assess the relationship between shock index and severity of bleeding, we will correlate shock index values, heart rate, and blood pressure measures to blood loss levels that will be recorded at 15, 30, 45, and 60 minutes following delivery. Absolute values and measured changes in these values during the first hour following delivery will be analyzed. We will also explore associations between these clinical signs/symptoms with other PPH outcomes, including provision of additional interventions to control bleeding, blood transfusion, and other severe outcomes.

Data will be owned by Gynuity Health Projects. The principal investigators and study coordinators will work together to analyze the results of the study and prepare at least one manuscript for submission to one or more relevant peer-reviewed journals. In addition, members of the study team will present the results of the study at conferences and meetings where appropriate. All principal investigators will be named along with key Gynuity staff as authors of any publications or presentations describing results from the study.

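### Controlling for other AMTSL components conditions on care given after allocation; if that care follows early bleeding, the adjusted primary estimates are biased, in a direction the protocol does not settle

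*Protocol*

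**What the plan says.** The study description in the protocol's Background, given in Spanish and in English, commits to an adjustment: "The practice of other AMTSL components will be documented and controlled for in our analysis". No other adjustment variable is named anywhere in the protocol.

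The timing comes from three other places:

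- **Allocation** (Randomization and Enrollment): "During the second stage, prior to each woman’s delivery, study personnel will open the next sequential randomization packet".
- **Study drug** (Intervention): given "according to randomization assignment as soon as possible after delivery of the baby".
- **Components** (Randomization and Enrollment): staff "will record any intervention, including other AMTSL components performed during delivery".

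The analysis section says what the components are, but there it speaks only of recording them: "We will register use of any other AMTSL components, such as controlled cord traction, uterine massage, etc. that are used". It also gives the regression plan: "Unadjusted and adjusted logistic regression will be conducted respectively for categorical and continuous dependent variables". It has no covariate list and does not say which estimate is primary.

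**The concern.** A covariate in a randomised comparison is safe when the assigned treatment cannot have changed it. Cord traction and massage do not meet that condition here. They come after allocation, the provider decides on them, and they fall inside the period in which the outcome accumulates. A provider who massages more because the uterus is soft or bleeding is heavy turns component use into a marker of blood already lost. If early loss differs by route, holding component use fixed compares women who are no longer alike by randomisation.

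Blinding does not prevent this. A provider who does not know the arm can still react to bleeding that differs by arm. Nor is there confounding for the adjustment to remove, since randomisation balances provider habit in expectation.

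At stake is which number answers the primary question. The first research question asks about route when oxytocin is given within AMTSL. That is the total effect of assignment with the components used as they happen to be used.

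**Working it through.** **Order of events**

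| Step | When | Protocol section |
|---|---|---|
| Packet opened | Second stage, before birth | Randomization and Enrollment |
| Blood collection starts | Immediately after birth; "blood loss will be measured in a calibrated container for 1 hour" | Intervention |
| Oxytocin and placebo given | As soon as possible after birth | Intervention |
| Other components performed and recorded | During delivery, after allocation | Randomization and Enrollment |

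Nothing in this order makes the components baseline variables, and their use is not fixed by the protocol.

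**What sets the direction.** For mean blood loss in a linear model, with differences taken as IV minus IM, least squares gives exactly

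adjusted difference = unadjusted difference − γ × δ,

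where δ is the IV minus IM difference in the proportion receiving the component, and γ is the component's coefficient in the adjusted model. When women who bleed more receive the component more often, γ tends to be positive. The sign of δ then decides the direction: toward zero if the IM arm bleeds more early, away from zero if the infusion arm does.

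**Size, by illustration.** The protocol gives no rate of component use, so there is no figure to reproduce. The only figures taken from it are the 50 ml design difference and, for scale, the mean of 275 ml and SD of 175 in the sample size section. Everything else is assumed. With A = 1 for IV and U, e₁, e₂ independent standard normal:

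- early loss = 150 − 50sA + 90U + 50e₁
- logit P(component) = log(0.3/0.7) + k(early − 150 + 25s)/100
- late loss = 125 − 50(1 − s)A + 60U + 50e₂ + θ × component

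Here s is the share of the 50 ml benefit that occurs early, k is the responsiveness of use per 100 ml of early loss, and θ is the component's own effect in ml. Each scenario has 1,000,000 women. Total SD came out at 155 to 169 ml. The IM mean is set at 275 without the component, whereas the protocol assigns 275 to IV; the level does not affect a linear difference.

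| s | k | θ | Use IM / IV | Unadjusted (ml) | Adjusted (ml) | Ratio |
|---|---|---|---|---|---|---|
| 0.5 | 0 | 0 | 29.9% / 30.0% | −49.4 | −49.4 | 1.00 |
| 0.5 | 1 | 0 | 35.5% / 30.9% | −50.0 | −43.8 | 0.88 |
| 0.8 | 0.5 | 0 | 33.1% / 28.9% | −50.5 | −47.3 | 0.94 |
| 0.8 | 2 | 0 | 43.3% / 32.0% | −50.4 | −28.7 | 0.57 |
| 0.8 | 2 | −50 | 43.5% / 32.1% | −44.8 | −28.5 | 0.64 |
| 0 | 2 | 0 | 37.6% / 37.7% | −50.0 | −50.2 | 1.00 |
| −0.3 | 0.5 | 0 | 30.3% / 31.8% | −49.8 | −51.0 | 1.02 |
| −0.6 | 2 | 0 | 33.4% / 41.9% | −50.3 | −66.6 | 1.33 |

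The last two rows have 15 and 30 ml more early loss under infusion (50 × 0.3 and 50 × 0.6).

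**Check against the identity.**

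- Fourth row: δ = 0.320 − 0.433 = −0.113, so γ = (−50.4 + 28.7)/(−0.113) ≈ 192 ml.
- Last row: δ = 0.419 − 0.334 = 0.085, so γ = (−50.3 + 66.6)/0.085 ≈ 192 ml.

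The component coefficient is the same in both. Only the sign of δ changed, and the bias changed sides with it.

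**Ranges.** With 50–80% of the benefit early and responsive use, the ratio was 0.57 to 0.99. With more early loss under infusion and θ = 0, it was 1.02 to 1.33 here, and up to 1.35 under slightly different assumptions. With no dependence on bleeding, or no early difference by route, it was 1.00. The runs cover mean loss only. The same reasoning applies to the proportion losing 500 ml or more, but its size was not computed.

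**The case against.** Four points on the other side have force.

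**A valid estimate is planned.** The analysis section lists plain comparisons between arms as its main analyses and mentions unadjusted models. A reader might infer that the randomised comparison is lost, or, from the word respectively in the regression sentence, that mean blood loss gets only an adjusted model. Neither inference is safe. That sentence also assigns logistic regression to continuous outcomes, so it is too garbled to carry a literal reading. What stands is that neither estimate is named as primary. A covariate list could be left to an analysis plan, but this protocol has already stated an adjustment rule.

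**Responsive use is not documented.** No section says that traction or massage is used more when bleeding is heavy. AMTSL is presented as preventive, and interventions to manage bleeding are listed separately as outcomes, so reactive massage might be recorded there. This makes the bias conditional. It does not remove it, because nothing in the protocol separates routine from reactive use of a component.

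**The direction is open.** A reader might infer that adjustment must shrink the effect. The Background gives onset 2–4 minutes after IM injection but a gradual response to infusion, with steady state at 15–40 minutes. The infusion arm could therefore bleed more early, which would push the adjusted estimate away from zero.

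**Adjustment could serve a purpose.** A component that predicts loss but is unrelated to early bleeding would add precision. The authors also cite an unpublished analysis suggesting that route matters most when oxytocin is the only component. That second interest is effect modification, and a main-effect covariate does not address it.

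**Conclusion.** The point holds as a flaw in a stated analysis rule. The protocol commits to controlling for variables that arise after allocation, at the provider's discretion, during outcome measurement, and it does not keep that model out of the primary comparison.

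The bias depends on two conditions that the document neither states nor excludes: component use responds to early bleeding, and early bleeding differs by route. If both hold, the adjusted difference in mean loss could plausibly be anywhere from 57% to about 135% of the unadjusted one under the assumptions shown. If either fails, that mechanism produces no bias. These figures show what is possible and do not estimate what will happen in this trial. The document does not support saying that adjustment will remove part of the effect, or that no valid estimate will be available.

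The edit is small and should be made before unblinding, so that two competing estimates of a primary outcome are not chosen between once the results are known.

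**What to change.** 1. **Background**, Spanish and English: replace the commitment to control for the components with: *Use of other AMTSL components will be documented and reported by arm.*
2. **Analysis and Dissemination of Results**: add: *The primary comparison for each primary outcome is unadjusted, or adjusted only for variables recorded before the randomisation packet is opened. Any model that includes AMTSL components is exploratory.* Choose one of the two options and name it.

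Suitable covariates already described are pre-delivery hemoglobin and obstetric history. Induction or augmentation qualifies only if begun before allocation: the packet is opened in the second stage, and the protocol allows for augmentation continuing until the fetal head is delivered. Parity and multiple pregnancy are not named as form fields, so confirm that they are captured before listing them.

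The cost is a few sentences, with no new data and no change to care. The one statistical downside is a possible small loss of precision if component use predicts blood loss but is unrelated to early bleeding.
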